# Regenerative Therapy for Liver Cirrhosis Based on Intrahepatic Arterial Infusion of Autologous Subcutaneous Adipose Tissue-Derived Regenerative (Stem) Cells: Protocol for a Confirmatory Multicenter Uncontrolled Clinical Trial

**DOI:** 10.2196/17904

**Published:** 2020-03-31

**Keywords:** adipose tissue-derived regenerative (stem) cells, stromal cells, stem cells, liver cirrhosis, investigator-initiated clinical trial protocol, adipose tissue dissociation device, protocol, stem cell therapy, liver

## Abstract

**Background:**

Liver cirrhosis results from chronic hepatitis, and is characterized by advanced fibrosis due to long-term hepatic inflammation. Cirrhosis ultimately leads to manifestations of jaundice, ascites, and encephalopathy, and increases the risk of hepatocellular carcinoma. Once cirrhosis is established, resulting in hepatic failure, no effective treatment is available. Therefore, novel therapies to inhibit disease progression of cirrhosis are needed.

**Objective:**

The objective of this investigator-initiated clinical trial is to assess the safety and efficacy of autologous adipose tissue-derived regenerative (stem) cell therapy delivered to the liver via the hepatic artery in patients with liver cirrhosis.

**Methods:**

Through consultation with the Japan Pharmaceuticals and Medical Devices Agency, we designed a clinical trial to assess a therapy for liver cirrhosis based on autologous adipose tissue-derived regenerative (stem) cells, which are extracted using an adipose tissue dissociation device. The primary endpoints of the trial are the serum albumin concentration, prothrombin activity, harmful events, and device malfunction.

**Results:**

Enrollment and registration were initiated in November 2017, and the follow-up period ended in November 2019. Data analysis and the clinical study report will be completed by the end of March 2020.

**Conclusions:**

Completion of this clinical trial, including data analysis, will provide data on the safety and efficacy of this novel liver repair therapy based on autologous adipose tissue-derived regenerative (stem) cells using an adipose tissue dissociation device.

**Trial Registration:**

UMIN Clinical Trials Registry UMIN000022601; https://tinyurl.com/w9uqw3q

**International Registered Report Identifier (IRRID):**

DERR1-10.2196/17904

## Introduction

### Background

Liver cirrhosis is the eventual outcome of chronic liver diseases, including chronic hepatitis, autoimmune hepatitis, primary biliary cholangitis, alcoholic hepatitis, and nonalcoholic steatohepatitis (NASH), which is currently increasing in prevalence relative to other liver conditions and is associated with metabolic disease [1,2]. Liver cirrhosis leads to various complications, including esophageal varix, hepatic encephalopathy, ascites, jaundice, and hepatocellular carcinoma, which result in a worse prognosis for patients with cirrhosis [3]. The end stage of cirrhosis is hepatic failure, for which liver transplantation is the only treatment as an extremely invasive procedure that requires continuous immunosuppressive therapy for the remainder of the patient’s life. Moreover, there are very few cadaveric donors in Japan, with only 69 cadaveric donors (and 347 living donors) for liver transplantation available in 2017 [4]. Therefore, novel treatments for cirrhosis should be explored.

Fatty liver disease and NASH are emerging chronic liver diseases. Although steatohepatitis is strongly correlated with metabolic syndrome, it is not clear why steatosis of the liver causes chronic inflammation and ultimately leads to cirrhosis [5].

### Objectives

Mesenchymal stem cells are somatic pluripotent stem cells that can differentiate into various cell types [6,7] and have immunomodulatory capabilities [8]. Freshly isolated adipose tissue is a rich source of mesenchymal stem cells [9]. Similar to bone marrow cells, autologous mesenchymal cells can be used therapeutically. Therefore, freshly isolated autologous adipose tissue-derived stromal cells have attracted substantial attention for potential therapeutic use in various organs [10]. We previously conducted a clinical study to confirm the safety of a liver cirrhosis therapy based on adipose tissue-derived stromal cells [11]. To determine the practicality of this treatment strategy, we designed an open-label, uncontrolled multi-institutional clinical trial for a regenerative therapy for liver cirrhosis based on adipose tissue-derived regenerative (stem) cells (ADRCs). This trial was designed to assess the safety and efficacy of the treatment in consultation with the Japan Pharmaceuticals and Medical Devices Agency (PMDA). Herein, we describe the detailed protocol for the trial.

## Methods

### Study Objectives

The objective of the study is to assess the efficacy and safety of an autologous ADRC therapy delivered to the liver via the hepatic artery.

### Study Design and Enrollment

This is a multicenter, collaborative, nonblinded, uncontrolled clinical trial carried out in Japan (Kanazawa University Hospital, Osaka Medical College Hospital). The adipose tissue dissociation device used to isolate ADRCs is the investigational trial device. All patients who meet the eligibility criteria and provide informed consent will be enrolled (Figure 1). Multimedia Appendix 1 shows the detailed schedule of the clinical study.

**Figure 1 figure1:**
[figure not shown]
Case enrollment procedure. This trial will enroll patients with nonalcoholic steatohepatitis or fatty liver disease who provided written informed consent. Regarding the steps indicated by the asterisk, screening and registration involve the following: nonalcoholic steatohepatitis patients who drink ≤20 g alcohol per day will simultaneously undergo the first and second screening stages, as well as provisional and definitive registration. Patients who drink >20 g but ≤70 g alcohol will undergo the initial screening and be provisionally registered. These patients are expected to restrict their alcohol consumption to ≤20 g per day for 8 weeks and then undergo the second screening stage. Patients meeting the enrollment criteria at this stage will be definitively registered to undergo the treatment described in this protocol followed by observation for 24 weeks after treatment. ADRCs: adipose tissue-derived regenerative (stem) cells.

### Eligibility Criteria

#### Inclusion Criteria

Patients who meet all of the following criteria are eligible for the study. A diagnosis of liver cirrhosis is obtained based on imaging or histological examination due to two types of etiology: NASH or fatty liver. NASH is determined according to the following criteria: alcohol intake ≤20 g/day, no other obvious liver injury etiologies, and association with complications such as obesity (especially visceral fat), metabolic syndrome, and diabetes mellitus. Fatty liver disease is determined according to the following criteria [12,13]: alcohol intake >20 g/day but ≤70 g/day (note that the criterion for the amount of alcohol consumed is the same for men and women in accordance with previous publications [12,13]; although the duration of alcohol drinking is not specified, most hepatologists assume that the patient has consumed the defined amount of alcohol for more than 5 years); no other obvious liver injury etiologies or association of complications such as obesity (especially visceral fat), metabolic syndrome, and diabetes mellitus; and ability to maintain alcohol intake at ≤20 g/day from the provisional registration until the second screening (≥8 weeks). Other eligibility criteria include age at the time of providing consent ≥20 years or older but <80 years, total bilirubin concentration ≤3.0 mg/dL at screening, platelet count ≥5.0×10^4^/µL at screening, prothrombin activity ≥70% at screening, serum creatinine level ≤1.5 mg/dL at screening, serum albumin ≤4.0 g/dL at screening, and patients able to provide written informed consent themselves.

#### Exclusion Criteria

Patients are excluded if they meet any of the following conditions: presence of severe pulmonary hypertension such as esophageal gastric varix, which poses a risk of rupture; presence of severe heart diseases, renal diseases, respiratory diseases, blood diseases, blood coagulation disorders, or other serious complications; presence or presumed presence of severe infectious diseases requiring intravenous treatment with antibiotics, antimycotics, or antiviral agents; presence of concurrent malignancy or history of malignancy within the past 5 years not deemed to be fully cured; history of cerebrovascular disease (eg, cerebral infarction, cerebral hemorrhage); known or suspected pregnancy; active treatment with adrenal corticosteroids; inability to maintain alcohol intake at <20 g/day after providing informed consent and for 24 weeks after treatment or discontinuation; treatment with other cell therapies within 6 months before providing informed consent; enrollment in other clinical trials; presumed life expectancy <1 year at the time of providing informed consent; allergy to drugs (eg, anesthetics) used in the trial; history of taking prohibited concomitant medications (antiplatelet drugs, anticoagulant drugs) within 7 days before providing informed consent; and judged to be inappropriate for enrollment by the principal investigator or subinvestigator.

### Treatment

Subcutaneous adipose tissue from the abdomen or buttock of the patient will be obtained by Tumescent liposuction, a standard cosmetic surgery method, under general anesthesia or local/lumbar spine local anesthesia. Regenerative (stem) cells will be isolated using the adipose tissue dissociation system Celution 800/IV (Cytori Therapeutics, San Diego, CA, USA), followed by measurements of cell number and viability in a collected cell aliquot using a nucleocounter (ChemoMetec, Gydevang, Denmark). Cell viability should be at least 70%. Cell aliquots will be prepared at a density of 1×10^6^/mL in Ringer’s lactate. ADRCs, at a density of 3.3×10^5^ cells/kg, will be administered through the common hepatic artery via the tip of microcatheter IV (Asahi Intec Co Ltd, Seto, Aichi, Japan), inserted subcutaneously into a femoral or upper arm artery. For 24 weeks after providing informed consent, albumin products, antiplatelets, and anticoagulants will be prohibited. The following drugs can be continued only when administered after informed consent has been provided: branched-chain amino acids, vitamin E, other nutritional therapies, hepatic protection drugs, and antihyperlipidemia drugs.

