### Follow up

The observation period after treatment will be 24 months during which examinations will be performed at various time points (Multimedia Appendix 1).

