### Regulatory Compliance

Approval of this clinical trial was obtained from the institutional review boards of Kanazawa University Hospital and Osaka Medical College Hospital. The study has been registered in the Japanese UMIN Clinical Trials Registry (UMIN000022601). This investigator-initiated clinical trial design was discussed with, and submitted to, the Japan PMDA before enrollment commenced. All treatment procedures in this trial will be carried out in accordance with the Declaration of Helsinki and International Conference on Harmonization Good Clinical Practice guidelines [16]. Written informed consent will be obtained from the patients before the first and second screenings as well as at registration.

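### The ban on albumin products is counted from consent but observation from treatment, so it ends before week 24 after treatment and may lapse before the albumin assessment

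*Protocol article*

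**What the plan says.** The protocol article sets several clocks.

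- **Ban on albumin products (Treatment):** "For 24 weeks after providing informed consent, albumin products, antiplatelets, and anticoagulants will be prohibited". The clock starts at consent.
- **Observation (Figure 1 caption):** patients are treated after definitive registration, "followed by observation for 24 weeks after treatment". The clock starts at treatment.
- **Observation (Follow up):** "The observation period after treatment will be 24 months". Same start, different length.
- **Consent (Regulatory Compliance):** "Written informed consent will be obtained from the patients before the first and second screenings as well as at registration". There is more than one consent date.
- **Run-in for patients drinking more than 20 g/day (Inclusion Criteria):** "ability to maintain alcohol intake at ≤20 g/day from the provisional registration until the second screening (≥8 weeks".
- **NASH patients drinking 20 g/day or less (Figure 1 caption):** they "will simultaneously undergo the first and second screening stages, as well as provisional and definitive registration". No interval to treatment is given.
- **Medication before consent (Exclusion Criteria):** "history of taking prohibited concomitant medications (antiplatelet drugs, anticoagulant drugs) within 7 days before providing informed consent". Albumin products are not on this list.
- **Alcohol limit (Exclusion Criteria):** it runs from consent to 24 weeks after treatment or discontinuation.

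The Sample Size section calls serum albumin a key efficacy endpoint. The Endpoints section gives no time at which it is assessed.

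**The concern.** Infused albumin raises serum albumin directly, and the protocol's own ban shows that the sponsor thought this worth controlling. The trial has no control arm, so a rise caused by an infusion could not be told apart from a rise caused by the cells. If the ban ends before the efficacy value is drawn, the key endpoint is unprotected at the point where protection is needed. With 8 patients, a single spurious responder carries great weight.

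The alcohol limit shows that a window ending at a fixed time after treatment was used elsewhere in the same protocol. The two windows differ and no reason is given.

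A secondary matter is the list of medication before consent. It omits albumin products, so an infusion shortly before consent is not screened out and could inflate the baseline value. That would bias the change in albumin against the therapy.

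**Working it through.** **Step 1: the plan's own figure.** The Sample Size section claims power over 85% with 7 patients, one-sided level .05, null rate 3% and expected rate 40%. The article states no rejection rule, so I take the smallest number of responders that keeps the exact binomial level at or below .05. One responder is not enough (level 0.192 at n = 7, 0.216 at n = 8). For two or more,

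P(X ≥ 2) = 1 − (1−p)^n − n·p·(1−p)^(n−1).

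| n | level at p = 0.03 | power at p = 0.40 |
|---|---|---|
| 7 | 1 − 0.97^7 − 7·0.03·0.97^6 = 0.017 | 1 − 0.6^7 − 7·0.4·0.6^6 = 0.841 |
| 8 | 1 − 0.97^8 − 8·0.03·0.97^7 = 0.022 | 1 − 0.6^8 − 8·0.4·0.6^7 = 0.894 |

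The exact power at n = 7 is 84.1%, about one point below the claim; a normal approximation gives 92.3%. That is close enough to take 2 responders as the implied rule.

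**Step 2: order of events.** Consent is taken before the first screening, before the second screening and at registration. The Figure 1 caption puts treatment after definitive registration. Every possible consent date therefore precedes treatment. Let g be the weeks from the consent that starts the ban to treatment. The ban ends at week 24 − g after treatment, and g weeks before week 24 are uncovered.

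**Step 3: size of g.**

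| Group and anchor | g (weeks) | Ban ends, week after treatment | Share of 24 weeks uncovered |
|---|---|---|---|
| >20 g/day, first consent | at least 8 (from the article) | 16 or earlier | at least 8/24 = 33% |
| NASH, or a later consent | not stated; 2 assumed | 22 | 2/24 = 8% |
| NASH, or a later consent | not stated; 4 assumed | 20 | 4/24 = 17% |

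If the 24 months in the Follow up section is meant (about 104 weeks), at least 104 − 24 = 80 weeks are uncovered in every patient. The abstract has enrollment starting in November 2017 and follow-up ending in November 2019. That leaves about 24 months for enrollment, run-in, treatment and observation together, which fits 24 weeks better, but the text does not settle it.

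**Step 4: consequence for the test.** Suppose one patient is counted as a responder only because of an infusion and all others respond at the null 3%. One further responder is then enough:

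- n = 8: 1 − 0.97^7 = 0.192, against 0.022 without the infusion.
- n = 7: 1 − 0.97^6 = 0.167, against 0.017.

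Two such patients would make rejection certain. These probabilities are conditional on the infusion having happened; the article gives no rate.

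**The case against.** The strongest reply is that no section says when albumin is assessed for efficacy, and the visit schedule is in an appendix that is not shown. With an assessment at week 12 and a gap of exactly 8 weeks, the ban (ending at week 16) would cover it. This stands. Week 24 is an inference from the 24-week observation, the imaging at 24 weeks and the 3-6 months of the earlier study. A reader might infer that infusions are allowed in the last weeks before the albumin endpoint. The article does not support that as fact, only that the ban may have lapsed by then.

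Second, the 8 uncovered weeks depend on counting from first consent. From consent at second screening or registration, the run-in falls before the clock starts and the uncovered time shrinks to an unstated interval. This also stands, but the ambiguity of the anchor is part of the problem.

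Third, the baseline point is narrow. The ban applies from consent, and consent precedes screening, so only an infusion shortly before consent could affect baseline, mainly in NASH patients. The exclusion list and the on-study ban also serve different purposes, so their difference is not in itself a contradiction.

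Fourth, the Treatment sentence may be condensed drafting of a window that matched the alcohol limit. That is plausible but cannot be shown from the text, which states a specific duration and a specific start.

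Finally, the handling of values after an infusion belongs to the analysis plan, which is not shown. Its absence here is therefore no fault. The fault is the mismatch of clocks, which the article does state.

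**Conclusion.** As written, the ban on albumin products ends before week 24 after treatment in every patient, because its clock starts at consent. This follows from the order of events alone. It is inconsistent with the alcohol limit, and the two stated lengths of observation contradict each other. The ban may lapse before the albumin assessment; whether it does depends on an assessment time the article omits.

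The uncovered time is at least 8 of 24 weeks for patients drinking more than 20 g/day if first consent starts the clock. Otherwise it equals the unstated interval from consent to treatment, for which 2-4 weeks is only an assumption. The rise in false-positive probability from 0.022 to 0.192 at n = 8 assumes the implied rule of 2 responders and one response due solely to an infusion.

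A reader might conclude that infusions took place or decided the result. Nothing in the article supports that; the finding is only that they are no longer prohibited. The omission of albumin products from the list of medication before consent is secondary. This should be fixed, and confidence is moderate.

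**What to change.** Reconcile the Figure 1 caption and the Exclusion Criteria, Treatment, Follow up and Regulatory Compliance sections so that the control of albumin products and the albumin assessment share one stated time origin. State which consent is meant and when albumin is assessed. Which restriction is clinically right is for the sponsor and investigators. Follow-up ended in November 2019, so this clarifies the record and cannot change conduct.

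Unless the analysis plan already has such a rule, add one before data fixation: albumin values after an albumin infusion are not counted as improvement, and the patient counts as a non-responder for the albumin response. A sensitivity analysis uses the last value before the infusion. If the data are already fixed, report the rule itself as a sensitivity analysis.

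The cost is a wording clarification, one analysis rule and a check of infusion dates in the concomitant-medication data of 8 patients. Sample size does not change. The responder rate may be slightly lower: if one of 8 patients is set to non-responder, the probability of at least 2 responders among the other 7 at the expected 40% is 0.841, against 0.894 for all 8. At the null 3% it is 0.017, so the false-positive probability stays below .05.

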### Endpoints

Efficacy endpoints are the serum albumin level and prothrombin activity. The safety endpoints are adverse reactions and device malfunction.

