### Sample Size

The serum albumin level is considered a key efficacy endpoint with respect to the proof of concept and mode of action of this treatment. In an earlier clinical study, we observed that 3 of 4 cirrhotic patients who underwent the same treatment as applied in this clinical trial had improved serum albumin levels after 3-6 months [11]. A sample size of 7 patients provided a power of over 85% with a one-sided significance level of .05 to reject the null rate of 3% under the expectation of 40%. This clinical trial was designed to explore safety and efficacy, and therefore a total of 8 patients was considered to be sufficient for this purpose.

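### As worded, the concomitant-drug rule does not exclude new starts of the listed nutritional and liver-directed drugs, in an uncontrolled trial whose key endpoint is serum albumin

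*Protocol article*

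**What the plan says.** The Treatment section of the protocol article sets two concomitant-drug rules, one after the other. The first is a plain prohibition with a window: "For 24 weeks after providing informed consent, albumin products, antiplatelets, and anticoagulants will be prohibited". The second is conditional: "The following drugs can be continued only when administered after informed consent has been provided: branched-chain amino acids, vitamin E, other nutritional therapies", and the list ends with "hepatic protection drugs, and antihyperlipidemia drugs".

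The Endpoints section says: "Efficacy endpoints are the serum albumin level and prothrombin activity". The Sample Size section ranks them: "The serum albumin level is considered a key efficacy endpoint with respect to the proof of concept and mode of action of this treatment". On design, Study Design and Enrollment says: "This is a multicenter, collaborative, nonblinded, uncontrolled clinical trial carried out in Japan".

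**The concern.** A drug can be *continued* only if the patient is already taking it, so a reader expects the condition to refer to use before consent or to a stable regimen. Instead it refers to administration after consent, and it says nothing about when use must have begun or whether the dose may change.

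This matters because efficacy is judged without a comparator. If a nutritional or liver-directed therapy is begun or increased after the albumin baseline, any rise in albumin from it falls in the same interval as any rise from the infused cells. Nothing in the design can separate the two.

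**Working it through.** **1. What the condition admits.** Four patterns of use, tested against the literal condition (given after consent):

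- In use before consent, carried on unchanged afterwards: condition met, and it fits the word *continued*.
- In use before consent, dose increased afterwards: condition met; dose is not mentioned.
- First started after consent: condition met, although it fits *continued* poorly.
- Stopped before consent: condition not met, but no rule is needed for a drug no longer given.

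The condition therefore excludes only the last pattern. For any drug actually given during the trial it restricts nothing.

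**2. Whether another section repairs it.** The Exclusion Criteria tie a drug rule to pre-consent use, with a 7-day window, but only for antiplatelet and anticoagulant drugs. No section bars new starts of the listed drugs, asks for a stable dose, or defines a baseline for them.

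**3. Timing.** Consent is not the albumin baseline. Regulatory Compliance places consent before the first screening, and again before the second screening and at registration, so consent is not a single date either. Patients in the higher alcohol group wait at least 8 weeks between provisional registration and the second screening. A drug begun soon after first consent could be established before infusion. The risk therefore lies only in starts or increases after the albumin baseline. How long that window stays open is also unclear: the Figure 1 caption has "followed by observation for 24 weeks after treatment", whereas Follow up has "The observation period after treatment will be 24 months".

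**4. Illustration of size.** Inputs from the Sample Size section: null rate 3%, expected rate 40%, one-sided level .05, 7 patients for the power statement, 8 planned. The smallest number of improvers that keeps to .05 is derived here; the article does not state it.

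Formula: P(X ≥ 2) = 1 − (1 − p)^n − n·p·(1 − p)^(n−1).

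The plan's own figure first:

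- One improver as the cut-off gives an error of 0.192 (n = 7) or 0.216 (n = 8), which is too high. Two is the smallest usable cut-off.
- Exact power, n = 7, p = 0.40: 1 − 0.0280 − 0.1306 = 0.841.
- Arcsine approximation: h = 2·asin(√0.40) − 2·asin(√0.03) = 1.021, and Φ(1.021·√7 − 1.645) = 0.855. This agrees with the stated power of over 85%; the exact value is just below it.
- Exact error at 3%: 0.0171 (n = 7), 0.0223 (n = 8). Exact power for n = 8: 0.894.

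Then the same cut-off with a higher improvement rate in the absence of any cell effect. Every rate above 3% is an assumption:

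| Background rate | n = 7 | n = 8 |
|---|---|---|
| 3% (plan) | 1.7% | 2.2% |
| 5% | 4.4% | 5.7% |
| 10% | 15.0% | 18.7% |
| 20% | 42.3% | 49.7% |

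The error stays within 5% only up to a background rate of about 5.3% (n = 7) or 4.6% (n = 8). These rates are averages over all patients. Moving from 3% to 10% requires that the share of patients starting a listed drug, multiplied by the added chance of improvement in each, equals 7 percentage points: for example, half the patients at 14 points each (0.5 × 14 = 7).

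**The case against.** A reader might infer that the sentence contradicts itself and that stable pre-consent use is forbidden. The text does not support that. A drug taken before consent and still given after it satisfies both the verb and the condition. The sentence says administered, not first administered.

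A reader might also infer that the rule positively authorises new starts. It is phrased as a limit on continuing, so the supportable statement is weaker: new starts are not excluded. It may be no more than a translation slip.

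A third tempting inference is that the false-success risk in this trial is 19% to 50%. That range rests on background rates of 10% to 20% that appear nowhere in the documents, and on a two-improver rule that they do not state. Nor do they say that these drugs raise albumin or that any patient began one. Being on the list is weak evidence of an effect on the endpoints, since the list also holds vitamin E and lipid-lowering drugs. The most direct confounder, albumin products, is prohibited outright for 24 weeks from consent.

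It can also be said that the article condenses a fuller protocol, that medication recording belongs there or in the analysis plan, and that follow-up ended in November 2019, so the wording can no longer affect which drugs were given.

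All of this limits the point without removing it. A rule that is printed and does not do what a restriction should do is a misstatement, not an omitted detail. The correction of the text and the analysis are what remain open.

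**Conclusion.** The point holds in a limited form. The condition on the listed drugs is met by anything given after consent, so as worded it does not keep out new starts or dose increases, and nothing else in the article does. With no control arm and albumin as the key endpoint, such a change after baseline could not be told apart from an effect of the cells.

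The size of any bias cannot be derived from the documents. The calculation shows only that a small trial with a 3% null rate has little room: its nominal 5% error would be exceeded once the background improvement rate passed roughly 5%. That rests on the inferred two-improver cut-off and on assumed background rates, and it should not be used to grade the seriousness of the point. The point deserves correction because the wording defect is plain and the protection is cheap.

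**What to change.** 1. Reconcile the sentence in the Treatment section with the approved protocol, so that it is clear when use of a listed drug must have begun and whether dose changes are covered. Which concomitant-drug rule is right is for the sponsor to state.
2. In the statistical analysis protocol, which the Statistical Analysis section says will be designed before the data are fixed, name the albumin baseline and the efficacy visit. Specify that patients with a new start or dose increase of a listed drug between those two dates are identified from the concomitant-medication records.
3. Add a sensitivity analysis of the albumin and prothrombin results that excludes these patients or counts them as not improved. The primary analysis need not change; treating such patients as not improved there is a debatable choice and is not asked for. If the data are already fixed, the analysis should be labelled post hoc.

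Cost: one corrected sentence, a little more analysis work from medication dates, and possibly a less favourable sensitivity result. With 8 patients, excluding even one or two leaves very little data, so the result should be read descriptively.
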